**Methods:**

Randomized controlled trial study with economic evaluation. Inclusion criteria are woman (biological), aged ≥ 18 years old and with a report of SUI ≥ once/week. Exclusion criteria are presence of vaginal or urinary infection, virginity, being in the gestational or puerperium period, or neurological disease. Participants will undergo physical therapy assessment and intervention: anamnesis, pelvic floor muscle assessment by vaginal palpation and manometry (Peritron^TM^), questionnaires (Short-Form 6 Dimensions—Brazil (SF-6D), King's Health Questionnaire (KHQ) and King´s Health Questionnaire for Scoring Algorithm), health costs, and voiding diary. Participants will be randomly allocated into 3 groups: CG (control group), IG 1 (intervention group 1, PFMT), and IG2 (intervention group 2, PFMT + NMES). The statistical analysis will be performed by intention to treat, and multivariate analysis of mixed effects will be used to compare outcomes. Effect size measurements will be calculated and will be provided by Cohen’s *d* test. A significance level of 5% will be adopted. Additionally, the incremental cost-effectiveness and incremental cost-utility ratios will be used.

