Data related to the economic analysis in health costs may be considered a relevant tool to be evaluated during SUI treatment. Studies that aim to identify the cost-effectiveness and cost-utility of a specific intervention may be used by governments’ institutions during the decision-making regarding the best evidence-based intervention that may correct the public health problems according their direct finite resources [13]. In Brazil, there are no estimates regarding annual expenses for the treatment of UI. However, it is known that more than $16 billion are spent on UI treatment in the USA annually [14]. It is expected that the economic analysis may affect directly the development of new guidelines related to the clinical practice of health professionals who treat women with SUI.

Therefore, the primary aim of this study is to evaluate the effects of intravaginal NMES associated with the PFMT protocol on urinary loss and quality of life in women with SUI. The secondary aim is to evaluate the cost-effectiveness and cost-utility and pelvic floor muscle in women with SUI.

The hypothesis of the study is that both treatments (NMES associated with PFMT and PFMT) will present good effectiveness; however, considering greater cost-effectiveness, PFMT will be the best option.

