At the interview and physical assessment, the subjective interview record will be applied, which generates qualitative variables that will be presented as frequencies and percentages and quantitative variables that will be presented as minimum value, maximum value, mean, median, and standard deviation. One researcher will perform the vaginal palpation and the manometry assessment, as well as applied SF6-D, KHQ, King´s Health Questionnaire for Scoring Algorithm, health cost analysis form, and 24 h-voiding diary, which will result in quantitative scales that will be presented as minimum value, maximum value, mean, median, and standard deviation.At the end of treatment sessions, vaginal palpation and manometry will be repeated, as well as SF6-D, KHQ, King’s Health Questionnaire for Scoring Algorithm, health cost analysis form, and the 24 h-voiding diary, which will result in quantitative scales that will be presented as minimum value, maximum value, mean, median, and standard deviation.At the 1st to the 6th month of follow-up, the health cost analysis form will be applied, and at the 3rd and 6th month of follow-up, the SF6-D, KHQ, King´s Health Questionnaire for Scoring Algorithm, and health cost analysis form will be completed, which will result in quantitative scales that will be presented as minimum value, maximum value, mean, median, and standard deviation.At the end of the treatment, the ANOVA for repeated measurements will be applied to verify the effects of the three groups and the two stages (pre-treatment and re-assessment after finished the intervention protocol) and the interactions between them according the results related to the vaginal palpation, manometry, SF6-D, KHQ, King´s Health Questionnaire for Scoring Algorithm, health cost analysis form, and 24 h-voiding diary, if the residues present normality. If the residues do not present normality, a non-parametric test will be applied.At the end of the follow-up, the repeated measures ANOVA will be applied to verify the effects of the three groups and the eight stages (pre-treatment, re-assessment after finished the intervention protocol and 1, 2, 3, 4, 5, and 6 months of the follow-up) and the interactions between them considering the SF6-D, KHQ, King’s Health Questionnaire for Scoring Algorithm, health cost analysis form, and 24 h-VD, if the residues present normality. If the residues do not present normality, a non-parametric test will be applied.The cost-utility assessment will be performed by the quality-adjusted life years (QALY), which combines the length and quality of life into a single index number between 0 and 1, where 0 corresponds to a health state judged to be equivalent to death and 1 corresponds to optimal health [35, 36]. To conduct the statistical analysis, the mean between-group cost differences will be corrected for their baseline, and the total costs will be divided by the costs differences for incremental analysis of cost-effectiveness and cost-utility ratios. Subsequently, a deterministic cost-utility value and a probabilistic one will be determined by applying a bootstrapping technique of 5000 interactions and the bias-corrected, in order to compare health costs between groups. The results will be presented with the confidence interval of 95% (95% CI). The likelihood of the cost-effective intervention will be estimated by the cost-effectiveness acceptability curves to compared values other than willingness to pay [37]. The Kaplan-Meier method and the Log-Rank between-group comparison test will be applied in order to assess the sensitivity of the uncertainty of each parameter by assessing the changes in the results in the range of parameter values [38].

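### A bias-corrected bootstrap 95% CI for the cost-utility ratio covers well below 95% if the IG2–IG1 QALY difference lies within about 1.5 standard errors of zero, which the protocol does not rule out

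*Protocol article*

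**What the plan says.** The abstract (Methods) names the economic estimands: "the incremental cost-effectiveness and incremental cost-utility ratios will be used". In the Statistical analysis plan, the cost-utility item takes QALYs as the effect measure and continues: "a deterministic cost-utility value and a probabilistic one will be determined by applying a bootstrapping technique of 5000 interactions and the bias-corrected". The purpose given in that sentence is a comparison of health costs between the arms. The sentence after it reads "The results will be presented with the confidence interval of 95% (95% CI"; it makes no exception for the ratio.

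The same item plans "cost-effectiveness acceptability curves to compared values other than willingness to pay".

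On what to expect, the Introduction's hypothesis is that "both treatments (NMES associated with PFMT and PFMT) will present good effectiveness; however, considering greater cost-effectiveness, PFMT will be the best option". The abstract's Discussion points the other way and hypothesises that the combined treatment will prove best. The contrast of IG1 with IG2 is among the planned post hoc contrasts. No expected QALY difference, QALY standard deviation, cost difference or cost standard deviation appears anywhere.

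**The concern.** An incremental cost-utility ratio divides a cost difference by a QALY difference. As the QALY difference passes through zero, the ratio jumps from plus to minus infinity, so ordering bootstrap ratios from smallest to largest no longer orders them from good to bad. With a positive cost difference, the most negative ratios (slightly worse at extra cost) and the largest positive ones (slightly better at extra cost) sit at opposite ends of the list, although they describe almost the same result. The bias correction uses the share of replicates below the point estimate to shift the limits. When replicates straddle zero, that share measures the jump rather than any bias, and the limits move to the wrong place.

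At stake is the stated precision of the ratio comparing supervised PFMT with and without NMES, which bears on the hypothesis about which treatment is the better option economically.

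**Working it through.** **Inputs from the protocol.** The sample size section gives 44 women per group, of whom 4 allow for loss, so 40 evaluable and 3 × 44 = 132 in total. The 40 per group can be reproduced as the between-group test of a repeated-measures ANOVA with f = 0.25, alpha 5% and power 85%, if one assumes three measurements correlated at 0.5 (neither is stated). The noncentrality is 0.25² × 120 × 3 / (1 + 2 × 0.5) = 11.25, giving power 0.851. Only n per arm matters below. The horizon is 10 weeks plus 6 months: 10/52 + 0.5 ≈ 0.69 year.

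**Assumed inputs.** QALY standard deviation 0.06, with 0.03–0.10 as the range; positive true cost difference.

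**Scale.** SE of the QALY difference = SD × √(2/n) = 0.06 × √(2/40) = 0.0134. Over SD 0.03–0.10 and n = 40–44, 1 SE is 0.006–0.022 QALY and 3 SE is 0.019–0.067 QALY. The latter is a sustained utility difference of about 0.03–0.10 over 0.69 year. A benchmark that needs no QALY SD: the design difference on the KHQ is 5/10 = 0.5 SD. A QALY difference as large in SD units would be 0.5/√(2/40) = 2.2 SE, and half of that 1.1 SE.

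**Why the bias correction misplaces the limits.** Suppose the observed QALY difference is 0.5 SE below zero, and treat the cost difference as fixed and positive.

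- Replicates with a negative QALY difference: Φ(0.5) = 0.69. These give the lowest 69% of the ratios, all negative.
- Share of ratios below the point estimate: Φ(0.5) − 0.5 = 0.19, so z₀ = −0.87.
- Upper limit at percentile Φ(2z₀ + 1.96) = Φ(0.215) = 0.585, still among the negative ratios.

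The 95% interval is then wholly negative and reads as costlier and worse, although 31% of replicates show IG2 as better.

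**Simulated coverage.** Cost difference over QALY difference, women resampled within arm, bias-corrected limits, nominal 95%. Two sets of runs were made: 600 trials × 1000 replicates with normal costs, cost difference 2 or 5 SE, cost–QALY correlation −0.3, 0 or 0.3; and 500 trials × 5000 replicates with skewed costs, cost difference 3 SE, 40 and 44 per arm.

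| True QALY difference | In QALYs (SD 0.06, n = 40) | Bias-corrected interval | Fieller interval |
|---|---|---|---|
| 0.1 SE | 0.0013 | 39–44% | 94–96% |
| 0.25 SE | 0.0034 | 48–51% | 93–96% |
| 0.5 SE | 0.0067 | 53–62% | 94–96% |
| 1 SE | 0.0134 | 71–76% | 93–97% |
| 1.5 SE | 0.0201 | 84% | 94% |
| 2 SE | 0.0268 | 90–93% | 94–97% |
| 3 SE | 0.0402 | 94–97% | 94–96% |

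**Pooling of opposite conclusions.** More than 2.5% of replicates fell on each side of a zero QALY difference in 80–95% of simulated trials when the true difference was within 1 SE of zero, and in 42–51% at 2 SE.

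**Alternatives under comparable inputs.** Bootstrap intervals for net monetary benefit covered 93–96%, and those for the cost difference 91–96%. The plain percentile interval for the ratio covered 93–98% from 0.5 SE upward but 51–61% at 0.1 SE.

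**The case against.** Several points against the concern carry weight.

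- **The interval may not be for the ratio.** The stated purpose of the bootstrap is to compare health costs, so the 95% CI could be meant for the cost difference, where it performs acceptably. This reading is admissible. But what the sentence bootstraps is the cost-utility value, and the text does not limit the interval to costs.
- **The failure is conditional.** A reader might infer that the interval is always far too narrow. It is not: coverage is about 90% at 2 SE and nominal near 3 SE.
- **The protocol does not predict equality.** A reader might take "both treatments (NMES associated with PFMT and PFMT) will present good effectiveness" to mean that a near-zero difference is what the trial expects. It says both work, not that they work equally, and the abstract expects the combination to be best. A near-zero difference is left open, no more.
- **Not every bootstrap interval fails equally.** Except very close to zero, the loss of coverage comes mainly from the bias correction. The ambiguous sign of the ratio remains with any method.
- **The acceptability curve survives.** Read literally, the curve sentence removes the willingness-to-pay axis, and a reader might conclude that no usable measure of decision uncertainty is left. The far likelier meaning is a range of willingness-to-pay values, in an article with other language slips. So read, the curve deals correctly with the sign of the QALY difference.
- **Joint resampling is not mentioned.** That is detail an article may leave to the full plan, and it is not counted as a fault here.

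The check also assumes the standard ratio. The text's own definition, by which "the total costs will be divided by the costs differences for incremental analysis of cost-effectiveness and cost-utility ratios", contains no QALY term; that is a separate matter, and correcting it would leave this one in place.

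**Conclusion.** The point holds in a limited form. If the planned interval is for the incremental ratio, the bias-corrected method is a poor choice for IG2 versus IG1. Coverage is about 40–85% when the true QALY difference is within 1.5 SE of zero, about 90% at 2 SE, and nominal near 3 SE. At an assumed QALY SD of 0.06, 1.5 SE is 0.020 QALY. Even a QALY effect as large in SD units as the KHQ design difference would be only about 2.2 SE. The interval may also combine replicates with opposite meanings.

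The sample size per arm comes from the protocol; the QALY and cost inputs are assumptions. The economic evaluation is a secondary outcome, the clinical contrasts are unaffected, and the planned acceptability curve softens the consequence. This should be corrected before analysis, but it is not a critical flaw.

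**What to change.** 1. Report the incremental ratio as a point value with the cost-effectiveness plane, and drop its bias-corrected interval. If an interval for the ratio is wanted, use Fieller's, accepting that it may be unbounded when the QALY difference is not clearly different from zero.
2. Draw the 5000 bootstrap samples from each woman's cost–QALY pair within arm. Report 95% CIs for the cost difference, the QALY difference and the net monetary benefit (willingness to pay × QALY difference − cost difference) over a willingness-to-pay range fixed before the allocation is revealed to the analyst.
3. Reword the acceptability-curve sentence so that it says the curve runs over a range of willingness-to-pay values.
4. If only the cost difference was meant to carry the bootstrap interval, say so.

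The cost is plan wording and a few lines of code, with no new data. The small downsides are that a willingness-to-pay range must be stated in advance and the headline interval per QALY is lost.

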
## Discussion

This study intends to demonstrate whether if SUI and urinary impact in quality of life decrease after a protocol treatment with home exercise guidance without physiotherapeutic supervision and after a protocol of PFMT alone or associated with intravaginal NMES supervised by one physiotherapist. In addition, it is expected that the present study demonstrate the effectiveness, cost-effectiveness, and cost-utility analysis of each proposed treatment. It will be seen in possible changes related to the SUI symptoms of after 10th treatment sessions and during a 6-month follow-up after the end of the treatment.

PFMT is a considered a technique with level of evidence A for the treatment of SUI. However, studies related to the NMES application during SUI are still inconclusive; however, it presents promising results in the treatment of SUI [10]. All the techniques mentioned in the present study are characterized as simple and with minimal occurrence of adverse effects, which facilitates the acceptance of therapy by women who need assistance. As the three groups included in the present study will be instructed to outperform a PFMT protocol daily at home, the addition of the group that will receive guidance only through the booklet will allow us to assess the true effectiveness of the association of PFMT and intravaginal NMES with professional physiotherapist supervision.

In addition, economic analyzes have been decisive in treatment options and may involve direct and indirect costs, with cost measures in monetary value. Then, we will conduct a study that will allow the identification of clinically important outcomes such as the general effectiveness or cost-effectiveness of NMES for SUI treatment in Brazilian women [39], items that are still not described in the previous literature [10].

According to a recently systematic review about scientific evidence of intravaginal NMES in SUI [10], one of the main findings was the low methodological quality of the studies, which may interfere with its reliability and application in clinical practice. Therefore, the present protocol can corroborate with the literature on the effects investigation of the intravaginal NMES associated with PFMT on SUI in addition to the identification of socioeconomic data.

After the conclusion of this research, the results will be presented in journals through peer-reviewed publications and scientific events, including the International Congress.

## Trial status

The protocol registration was approved on 3 September 2019 (it was updated and approved on February 24, 2020) and is at version 2. The initial recruitment date will be in January 2022, and the approximate date of completion of until the first semester of 2024.

## Data Availability

Not applicable.

## Abbreviations

UI: Urinary incontinence
UUI: Urgency urinary incontinence
SUI: Stress urinary incontinence
MUI: Mixed urinary incontinence
PFM: Pelvic floor muscles
PFMT: Pelvic floor muscle training
ICT: Informed consent term
LAMU: Laboratory of Research in Women’s Health
UFSCar: Federal University of São Carlos
ANOVA: Analysis of variance
KHQ: King’s Health Questionnaire
24 h-VD: 24 h-voiding diary
DMC: Data Monitoring Committee
SF-6D: *Short-Form 6 Dimensions*—Brazil
